### 2.8. Interventions

The TPS intervention venue will be located at the Integrative Health Clinic (IHC), the Hong Kong Polytechnic University. A licensed mental health practitioner (PI: [name]) will deliver the TPS intervention.

#### 2.8.1. Intervention TPS

The TPS system consists of a mobile single transducer and an infrared camera system, which incorporates neuro-navigation; this system was developed by NEUROLITH, Storz Medical AG, Tägerwilen, Switzerland. This TPS system can generate single ultrashort (3 µs) ultrasound pulses with 0.2–0.25 energy levels (mJ/mm^2^) and 2.5–4 Hz pulse frequencies (pulses per second). During the TPS session, participants will sit in an adjustable electronic chair and wear a BodyTrack system that consists of a tracking glass with markers, a 3D camera, and a TPS handpiece. The reasons for wearing this BodyTrack system are to ensure that participant’s heads match their own fMRI (T1 images) so that the interventionist can visualize each pulse applied and documented in real time. The real-time tracking of the handpiece position enables automatic visualization of the treated brain region, highlighted in green.

#### 2.8.2. Treatment Brain Region

We will target the right temporoparietal junction (rTPJ), a key node for social cognition, which is a typical area of difficulty among individuals with ASD [13]. We selected the treatment brain region based on previous research [4], which had demonstrated abnormal brain activation in ASD and can improve social communication in adolescents and young adults with ASD. In this study, we will deliver 800 pulses (confirmed with the NEUROLITH-TPS manufacturer, neurologist, and psychiatrist in the project team) in each TPS session to subject’s rTPJ. Each TPS session will take approximately 30 min to complete. The interventionist will manually move the TPS handpiece over the subject’s skull to visualize the TPS pulses in their T1 brain images. The treatment will be carried out by trained staff holding the applicator in their hand. All TPS treatment sessions will be recorded for individual evaluation of the intracerebral pulse localizations.

#### 2.8.3. Sham–Control TPS

The procedure for sham stimulation will be identical, except that the castor oil used in the TPS group will be replaced by air-filled stand-off cushion in the hand piece. This sham device will be able to produce similar sound and stimuli on the subject’s head. Participants will be asked to continue their routine medication regimen throughout TPS intervention period.

#### 2.8.4. Intervention Dose

All eligible participants will be randomized to receive 6 verum TPS treatment sessions or sham TPS, with 3 sessions per week on alternate days, and for two consecutive weeks. Each TPS session will last for 20 min. The outcome measurements will be assessed at baseline, immediately after intervention (2 weeks), and at 1-month and 3-month F/Us (Figure 1, CONSORT flow diagram).

### 2.9. Fidelity

The project team will ascertain whether the interventions are delivered as intended in the protocol. The interventionist (PI) obtained a PhD in Social Sciences (HKU) and is a UK and HK licensed mental health professional with more than 10 years’ clinical experience in mental health and neuroscience. The research associate will issue WhatsApp message reminders (e.g., TPS intervention schedule, fMRI scan appointments, and f/u appointments slips) to parents and monitor subjects’ progress, adverse effect, and adherence throughout the trial period.

### 2.10. Adverse Effects and Risk Indicators

A TPS adverse effect associated with TPS administration will be generated from existing literature to monitor tolerability and adverse events throughout the TPS intervention period. NIBS is also considered very safe for paediatric populations, as evidenced by a recent study findings that showed no adverse effects across 382 young children under 18 years [14].

### 2.11. Ethical and Data Security Considerations

Ethical approval will be sought from the Human Subjects Ethics Sub-committee, the Hong Kong Polytechnic University. This study adheres the ethical principle guidelines written by the Declaration of Helsinki developed by the World Medical Association. All eligible participants in this study will be covered by trial insurance. Potential risks associated with fMRI and TPS will be clearly indicated in the Information Sheet and written consent form. Right of withdrawal, voluntary participation, participant anonymity, and confidentiality will be respected. Since participants are <18 years old, their parents will have to provide written consent in this study.

### 2.12. Outcome Evaluation (Primary and Secondary Outcomes)

#### 2.12.1. Baseline Assessment

##### Demographic Data

The subjects’ basic demographic data, including age, gender, body mass index, years of education, birth history, number of siblings, financial condition of family, and family history of ASD, will be obtained. Subjects’ psychiatric history, age of diagnosis, medical health history, current treatment regime and compliance, and developmental history will be solicited by direct face-to-face interviews with the participants’ parents.

#### 2.12.2. Primary Outcome

The primary outcome will be assessed by the Childhood Autism Rating Scale (CARS). The CARS is a 15-item behavioural rating scale developed to identify autism and to examine its severity. The 15 items include different domains (e.g., relating to people, imitative behaviour, emotional response, body and object use, adaptation to change, visual/listening/perceptive response, fear or anxiety, verbal/nonverbal communication, activity level, consistency of intellective relations, and general impressions [15]. Total scores range from 15 to 60; scores below 30 indicate non-autistic range, scores between 30 and 36.5 indicate mild to moderate autism, and scores from 37 to 60 indicate severe autism [16]. The assessment tool is well-validated and has been widely used in various studies. CARS will be assessed at baseline, immediately after post-stimulation at week 2, and at 1-month, and 3 months post-stimulation follow-up.

#### 2.12.3. Secondary Outcomes

##### Autism Spectrum Quotient (AQ)—Adolescent Version

It is a self-report instrument for autistic traits. The AQ score ranges from 0 to 50. AQ is made up of 10 questions assessing (1) social skill, (2) attention switching, (3) attention to detail, (4) communication, and (5) imagination [17].

##### The Social Responsiveness Scale (SRS)

SRS is an instrument measuring the continuum of autism symptom severity, which is commonly used in children and adolescents between the ages of 4 and 18 years [18]. SRS consists of 65 items subsumed in five “a priori” content areas of social deficits, i.e., social awareness, social cognition, social communication, social motivation, and autistic mannerisms. Parents rate each item on a 4-item Likert scale (0–4). The higher the scores, the more severe the social deficits. Multiple studies have demonstrated that the SRS has satisfactory reliability and validity for measuring autism symptoms in individuals < 18 years of age [19,20].

##### Australian Scale for Asperger’s Syndrome (ASAS)

ASAS is used to screen the behaviours and abilities indicative of Asperger’s syndrome in subjects older than 6 years old [21]. It has 25 items, and parents/teachers/professionals who know the child can rate these aspects using the Chinese version.

##### Faux Pas Recognition Test (FPRT)

It is a very common advanced test to measure the theory of mind and social cognition [22].

##### Stroop Test

It is a neuropsychological test commonly used to assess the inhibition control component of executive function. It tests the subject’s ability to inhibit cognitive interference that occurs when the processing of a specific stimulus feature impedes the simultaneous processing of a second stimulus attribute [23].

##### Working Memory

The working memory of participants will be measured with the memory span tasks (both forward and backward digit recall). The digit span test has been used previously to assess working memory in school-aged children with ASD in Hong Kong.

##### Clinical Global Impression—Severity and Improvement Scale (CGI-S and CGI-I)

CGI-S is a 7-point clinician rating scale based upon observed and reported symptoms, behaviour, and function in the past seven days. Clearly, symptoms and behaviour can fluctuate over a week; the score should reflect the average severity level across the seven days. CGI-I requires the clinician to assess the extent to which the subject’s illness improved or worsened, when compared to baseline before the intervention. The two rating scales are usually used as a combination to supplement each other [24].

##### Neuroimaging

Participants will have to undergo neuroimaging twice (pre-and posttreatment MRI) to evaluate any changes in structural and functional brain connectivity changes. Structural MRI, DTI, and rs-fMRI were taken using a 3T Tesla scanner at The Hong Kong Polytechnic University. The whole scan will take about 45 min. Structural MRI scans (T1) will be used to assess regional volume differences across the whole brain. High-resolution sagittal 3D T1-weighted (MPRAGE) images of 1 × 1 × 1mm will be acquired with repetition time (TR) = 1820 ms, echo time (TE) = 3.75 ms, inversion time (TI) = 1100 ms, and flip angle = 70°. DTI sequencing will be conducted using single-shot spin-echo echo-planar imaging, with diffusion-sensitizing gradients applied along 16 non-collinear directions with diffusion weighting factor b = 1000 s/mm^2^, plus two b = 0 images. The imaging parameters will be TR/TE = 1200/82 ms, matrix size = 128 × 128, field of view (FOV) = 240 mm, slice thickness = 3 mm with no intersection gap, number of excitations = 2, and number of slices = 67.

The resting-state fMRI of 150 T2-weighted gradient echo planar imaging (EPI) will be acquired with 32 slices, with a resolution of 3 × 3 × 4 mm, and subjects will see a fixation cross (‘+’) passively at the centre of the screen. Image processing and analysis will be performed using FSL software packages (http://fsl.fmrib.ox.ac.uk/fsl/fslwiki/, accessed on 12 June 2022), and total brain an total grey matter will be extracted from the T1 structural scan. Voxel-based morphometry (VBM) will be used to segment and compare grey matter tissue maps and regional tissue density differences using [25]. Fractional anisotropy (FA) maps extracted from DTI imaging will be used to assess structural connectivity.

For evaluating functional connectivity, all resting state-fMRI (rs-fMRI) volumes will be pre-and post-processed, with motion correction and slice timing correction, and linearly registered to the Montreal Neurological Institute (MNI) standard space. The Rs-fMRI data analysis will use a data-driven approach. Multivariate Exploratory Linear Decomposition in FSL will be used to conduct an independent component analysis. A set of independent components will be identified as common resting-state functional networks. The global and local efficiency, modularity, and hubs will be computed using the Brain Connectivity Toolbox (https://sites.google.com/site/bctnet/, accessed on 12 June 2022). Between-group differences in the individual functional networks will be analysed by a dual regression approach. The significance threshold of the voxel-wise differences will be set at *p* < 0.05.

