#### 1.2.2. Secondary Hypotheses

Participants in the verum TPS group will have significant improvement in the Autism Spectrum Quotient (AQ) compared with the sham TPS group, which will be maintained at the 1-month and 3-month follow-ups.Participants in the verum TPS group will have significant improvements in the Social Responsiveness Scale (SRS) compared with the sham TPS group, which will be maintained at the 1-month and 3-month follow-ups.Participants in the verum TPS group will have significant improvement in the Faux Pas Recognition Test compared with the sham TPS group, which will be maintained at the 1-month and 3-month follow-ups.Participants in the verum TPS group will have significant improvement in the Stroop test compared with the sham TPS group, which will be maintained at the 1-month and 3-month follow-ups.Participants in the verum TPS group will have significant improvement in the Clinical global impression—severity and improvement scale (CGI-S and CGI-I) compared with the sham TPS group, which will be maintained at the 1-month and 3-month follow-ups.Participants in the verum TPS group will have significant brain function connectivity changes at posttreatment fMRI and resting-state MRI compared to the sham TPS group, which will be maintained at the 1-month and 3-month follow-ups.

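### Only linear registration is named for bringing the resting-state scans into standard space before a voxel-wise verum-versus-sham comparison; this may cost sensitivity on a secondary outcome (minor)

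*Protocol article*

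**What the plan says.** The Neuroimaging part of section 2.12.3 sets out the resting-state chain. After motion and slice-timing correction, volumes are "linearly registered to the Montreal Neurological Institute (MNI) standard space". The analysis strategy is then given: "The Rs-fMRI data analysis will use a data-driven approach". Independent components are identified as functional networks and graph measures are computed. For the comparison of arms, "Between-group differences in the individual functional networks will be analysed by a dual regression approach". The last sentence, which begins "The significance threshold of the voxel-wise differences will be set at", puts that threshold at p < 0.05.

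The same part gives the acquisition, "with a resolution of 3 × 3 × 4 mm" for the resting-state images, and a 1 × 1 × 1 mm T1 scan. On software it says "Image processing and analysis will be performed using FSL software packages".

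The comparison serves the third aim in section 1.1 and a secondary hypothesis in section 1.2.2, which expects "significant brain function connectivity changes at posttreatment fMRI and resting-state MRI compared to the sham TPS group". The stimulation site is given in section 2.8.2: "We will target the right temporoparietal junction (rTPJ), a key node for social cognition".

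**The concern.** A voxel-wise test between arms assumes that a given voxel holds the same anatomy in every participant. A linear (affine) transform in three dimensions has at most 12 parameters for the whole brain. It matches position, orientation, size and overall shape, but not the individual folding of the cortex. What remains unmatched lowers the group-average effect at its centre and spreads it over neighbouring voxels.

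With 17 per arm there is little power to spare. The practical risk is that a real but local change in connectivity is reported as no difference. The stimulation is focal, so a local effect is plausible. A high-resolution T1 scan, which is what a non-linear alignment needs, is already planned for each participant.

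This is a method that the article states, so it can be questioned as stated. It is not a complaint that detail was left out.

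**Working it through.** **What the documents supply.** Registration type: linear, to MNI space. Test: voxel-wise dual regression, verum against sham, p < 0.05, sidedness not stated. Sample: 17 per arm (section 2.5). Voxel size: 3 × 3 × 4 mm. They give no registration error, smoothing kernel, spatial extent of effect or imaging effect size, so the plan has no figure of its own on this point to reproduce.

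**Reference effect.** The only design figure is the total of 34, which is not derived for imaging. Two-sided 0.05 and 80% power are assumed here, since section 2.5 states neither. The stated effect size of 0.5 then gives 34 by the exact t-test if read as Cohen's f (d = 1.0), and 128 if read as Cohen's d. I use d = 1.0 below as the more favourable illustration. It is not an estimate of the imaging effect.

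**Model (all inputs assumed).**
- The effect is a three-dimensional Gaussian with SD s0 = FWHM / 2.355.
- Residual misalignment is Gaussian with SD s per axis.
- The share of the peak kept in the group average is (s0² / (s0² + s²))^1.5. The between-participant SD is held fixed.
- Power is for one two-sample t-test at the peak voxel, two-sided 0.05, 32 df, non-centrality d × share × √(17/2). There is no smoothing and no multiplicity correction.
- Take s = 2 mm for non-linear and 3 to 4 mm for linear alignment.

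Example: FWHM 12 mm gives s0 = 5.096 and s0² = 25.96. With s = 3, the share is (25.96 / 34.96)^1.5 = 0.640 and power is 44.0%. With perfect alignment, power is 80.7%.

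| Focus FWHM | Share kept at 2 / 3 / 4 mm | Power (%) at 2 / 3 / 4 mm | Loss against 2 mm (points), at 3 / 4 mm |
|---|---|---|---|
| 12 mm | 0.807 / 0.640 / 0.487 | 62.6 / 44.0 / 28.0 | 18.6 / 34.6 |
| 15 mm | 0.868 / 0.740 / 0.607 | 69.0 / 55.3 / 40.4 | 13.7 / 28.6 |
| 20 mm | 0.922 / 0.838 / 0.740 | 74.1 / 65.9 / 55.3 | 8.2 / 18.8 |
| 30 mm | 0.964 / 0.922 / 0.868 | 77.8 / 74.1 / 69.0 | 3.7 / 8.8 |

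**Smaller effect.** With d = 0.5, power is 29.3% under perfect alignment. For a focus of 12 to 15 mm it is 20.7 to 23.3% at 2 mm and 14.8 to 18.2% at 3 mm. Alignment matters less here because power is low either way.

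**Reading.** The direction is the same throughout. The size depends on the assumed width of the effect, the assumed gain in alignment and the assumed d. Even the 2 mm case falls short of 80.7%, so non-linear alignment would recover only part of the loss.

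**The case against.** The strongest reply is that the sentence compresses a whole pipeline. It also leaves out smoothing, temporal filtering and the step from functional to T1 images, all of which an article may leave to a fuller imaging plan. That stands in part: a reader might infer that linear registration is the sole alignment step, but the text does not say so. It does name the type of registration. If a non-linear step is also used, the description is incomplete on a point it chose to specify; if not, a better method was available.

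A reader might also infer that the trial will miss an effect at the right temporoparietal junction. The documents do not support that. The junction is the stimulation target. The resting-state analysis works on data-driven networks, and no seed, region of interest or test at that site is described.

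The power model is also open to attack, and rightly. It takes one voxel at the exact peak, whereas the plan tests whole maps. Misalignment lowers the peak but widens the effect, the voxel size already limits localisation, and smoothing would narrow the gap between methods. The graph measures lie outside the calculation. The table therefore shows direction and sensitivity to assumptions; it does not estimate this trial's power.

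Finally, the consequence is limited. The step applies to all scans in both arms, and the outcome is secondary in what section 2.5 calls a pilot study. This argues for low priority and does not remove the point.

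**Conclusion.** The point holds as a minor one. The article names only linear registration before a voxel-wise comparison of 17 against 17, and such a transform cannot remove local anatomical differences, so the comparison may lose sensitivity. The documents do not allow the loss to be computed. In the illustration, 3 to 4 mm against 2 mm of misalignment costs about 14 to 35 points of single-voxel power for a focus of 12 to 15 mm, and about 4 to 9 points for one of 30 mm. All of these assume d = 1.0.

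It would be wrong to conclude that the maps are blurred by a known amount, or that non-linear registration would restore full power. Nor is a bias between verum and sham or an inflated type I error to be expected. The primary CARS analysis is not affected.

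**What to change.** In the Neuroimaging part of section 2.12.3, replace the linear registration clause with wording such as: *Each resting-state run will be registered to the participant's own T1 scan, and the T1 scan will be registered non-linearly to MNI space. The same T1-to-standard warp will be applied to that participant's pre- and post-treatment runs. Registration quality will be checked blind to arm.* Using one warp per participant keeps alignment from differing between the two time points. If a non-linear step is already intended, the same wording would make the article match the pipeline.

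The article names the software package but not its modules, so the team should confirm which tool will carry out the non-linear step. It should do so before allocation is unblinded, so that the choice cannot follow the results.

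The cost is extra computing and the checking of 34 × 2 = 68 runs. No new scans or visits are needed, because the T1 scan is already planned.

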### 2.5. Sample Size

Based on a similar RCT design (4), the estimated effect size of repeated transcranial magnetic stimulation is 0.5. Nonetheless, this study is the first study evaluating TPS on ASD. Hence, we hypothesize a small effect size (0.3) on this pilot study. We used G*Power 3.1.9.4 to estimate the sample size for this study. Considering a similar study using rTMS with an effect size of 0.5, we decided to use 0.5 effect size in this first study. Thus, the sample size required is 34 in this study (17 subjects in each group).

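### The voxel-wise connectivity maps are to be judged at p < 0.05 with no correction named over voxels or networks, so as written they cannot test the imaging hypothesis

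*Protocol article*

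**What the plan says.** The Neuroimaging part of section 2.12.3 describes the resting-state analysis in four steps.

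- The search is open: "The Rs-fMRI data analysis will use a data-driven approach".
- Independent component analysis in FSL supplies the networks: "A set of independent components will be identified as common resting-state functional networks". Their number is not given.
- The arms are then compared: "Between-group differences in the individual functional networks will be analysed by a dual regression approach".
- The decision rule follows: "The significance threshold of the voxel-wise differences will be set at" p < 0.05.

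The images themselves "will be acquired with 32 slices, with a resolution of 3 × 3 × 4 mm".

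These maps serve aim 3 (section 1.1) and the last secondary hypothesis (section 1.2.2), which expects "significant brain function connectivity changes at posttreatment fMRI and resting-state MRI compared to the sham TPS group". Section 3 sets a general 5% level. Its only multiplicity correction is Bonferroni for post hoc t-tests between assessment times.

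**The concern.** A voxel-wise comparison runs one test at every voxel of every network map. A 5% threshold at each voxel controls the error of that one test. It does not control the chance that some part of the brain looks different between arms. The article fixes the threshold itself, so this is a stated decision rule and not merely a detail left to a fuller document.

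Nothing else in the described connectivity analysis narrows the search. No seed, region or primary network is named for it, although stimulation is aimed at a single region, the right temporoparietal junction (section 2.8.2).

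An analyst who followed the text literally would have regions to report whether or not TPS does anything. A test that nearly always finds something cannot count as evidence for the connectivity hypothesis.

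**Working it through.** **Plan's own figure.** The threshold is a rule and not a derived number. One test at p < 0.05 has a 5% false-positive chance, and the article gives no error rate for a whole map, so there is nothing further to reproduce.

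**Inputs from the article.** Voxel size 3 × 3 × 4 mm; threshold 0.05 per voxel; 17 participants per arm (section 2.5).

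**Assumptions.** Brain volume 1.2–1.5 litres; two-sided tests; 6–20 networks. The article states none of these.

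**Step 1: expected false-positive voxels in one map with no effect.** Voxel volume = 3 × 3 × 4 = 36 mm³. Voxels = brain volume / 36. Expected false positives = 0.05 × voxels.

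| Assumed brain volume | Voxels | Expected false positives |
|---|---|---|
| 1.2 litres | 1,200,000 / 36 = 33,333 | 1,667 |
| 1.5 litres | 1,500,000 / 36 = 41,667 | 2,083 |

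At 1.0 litre the figures would be 27,778 voxels and 1,389 false positives. Correlation between neighbouring voxels does not change these expected counts.

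**Step 2: chance of at least one false positive in a map.** Correlation does matter here, because it reduces the effective number of independent tests, m. The chance is 1 − 0.95^m.

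| Effective tests m | Chance of at least one |
|---|---|
| 20 | 64% |
| 50 | 92% |
| 100 | 99.4% |

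Even a drastic reduction from more than 30,000 voxels to 20 effective tests leaves the error far above 5%.

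**Step 3: simulation with no effect.** Smooth random images were generated on the stated voxel grid (42,304 voxels in the mask, about 1.52 litres) and compared 17 versus 17 by two-sided t-test, with 60 runs at each smoothness.

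| Smoothness (FWHM) | Runs with any voxel at p < 0.05 | Median number of such voxels (range) | Runs with any voxel after Bonferroni over voxels |
|---|---|---|---|
| 6 mm | 60 of 60 | 2,109 (1,955–2,316) | 3% |
| 10 mm | 60 of 60 | 2,162 (1,712–2,450) | 5% |

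The Bonferroni cut-off was an absolute t above 5.97 on 32 degrees of freedom.

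**Step 4: networks.** Suppose each map were properly held at 5%. Over k independent networks the chance of a false finding in at least one is 1 − 0.95^k.

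| Networks k | Chance of at least one false finding | Level per network to hold 5% overall (0.05 / k) |
|---|---|---|
| 6 | 26% | 0.0083 |
| 10 | 40% | 0.005 |
| 20 | 64% | 0.0025 |

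Correction over voxels is therefore necessary but not sufficient if several networks are tested on equal terms.

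**The case against.** The strongest reply is that the article never uses the word uncorrected. A level of 0.05 may equally be meant for p-values already corrected over voxels, and a condensed article often leaves the inference method to a fuller imaging plan. This stands as far as intent goes. A reader might infer that the team has chosen uncorrected maps, but the document does not show that. What remains is that the article attaches the threshold to voxel-wise differences and commits to no correction, so following it literally gives the result above. If correction was intended, one phrase would say so.

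A reader might also infer that the imaging hypothesis is bound to be confirmed by chance. The article does not say that one voxel above threshold confirms it. It also plans global and local efficiency, modularity and hubs, which are not voxel-wise tests and are not touched by this calculation.

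A third tempting reading is that the analysis ignores change over time, because the dual-regression sentence mentions only differences between groups. The Neuroimaging text plans scans before and after treatment to evaluate change, and section 3 applies a time-by-treatment model to secondary outcomes. This is a gap in wording and does not show that change is left out.

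Finally, the analysis is secondary, in a study that calls itself a pilot. That limits the reach of the problem but does not make the threshold usable.

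**Conclusion.** The point holds for the voxel-wise dual-regression analysis as written. With no treatment effect, false-positive voxels are near-certain: about 1,700–2,100 per map at the stated voxel size, assuming a 1.2–1.5 litre brain. The simulation agrees, with such voxels in all 60 runs at each smoothness. The exact counts depend on brain volume, smoothness and the final image grid. A finer standard-space grid would raise them, but the article gives no such resolution and the conclusion does not need one. The number of networks is likewise assumed, and it affects only how much more correction is needed.

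The consequence is confined to the secondary connectivity hypothesis and aim 3, for which this analysis gives practically no false-positive control. The CARS primary analysis, the other clinical outcomes and the graph measures are unaffected.

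**What to change.** In the Neuroimaging part of section 2.12.3, change the threshold to p < 0.05 corrected for multiple comparisons over voxels, and name the method. Permutation-based family-wise error control in FSL is one suitable choice, since FSL is already the planned software; other recognised corrections would also do.

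Then deal with the networks in one of two ways: adjust for the number tested (for example Bonferroni or Holm), or name one network in advance as confirmatory and label the rest exploratory.

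State that the test applies to the between-arm difference in pre-to-post change.

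This takes two or three sentences and some computing time, and should be settled before unblinded images are analysed. Recruitment, scanning and treatment do not change. The price is that fewer regions will be called significant, and with 17 participants per arm only large differences may survive.
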